### Intervention

The goal of the intervention is that parents will brush their young children’s teeth and older children and adults will brush their own teeth twice a day with fluoridated toothpaste. Our strategies to promote this behavior reflect the integrative model of health behavior of Fishbein et al [21] and expansions by Michie et al, Michie et al, and Cane et al [22-24] (Table 1). These guides to the processes that govern health behavior were proven useful in a prior small-group intervention we designed, tested, and found to be successful to increase parents’ frequency of brushing their preschool-age children’s teeth. In that study of 67 families, the intervention components rated most highly by parents were the provision of free toothbrushes and toothpaste for all members of the family, hands-on instruction in how to brush a child’s teeth, and tips to overcome a child’s resistance and make toothbrushing “fun” [25]. In the formative work that led to the intervention’s design, we found parents who brushed their children's teeth twice a day were more likely to describe using specific skills to overcome barriers, have high self-efficacy for toothbrushing, and have high self-standards for establishing it as a routine. In contrast, parents who brushed their children's teeth less than twice daily were more likely to hold negative or false beliefs about the benefits of twice daily toothbrushing, report little normative pressure or social support for the behavior, have lower self-standards, describe more external constraints, and offer fewer ideas to overcome barriers [8].

**Table 1 table1:** Mapping of the components of the “Everybody Brush!” intervention to the theoretical domains, intervention functions, and behavior change techniques.

Intervention component			Theoretical domain	Intervention function	Behavior change technique
**Toothbrushing supplies (kit)**					
	7 toothpastes and 7 toothbrushes		Environmental resources	Enablement	Adding objects to the environment
**Toothbrushing supplies helpline**					
	Request more toothbrushing supplies by telephone		Environmental resources	Enablement	Adding objects to the environment
**Toothbrushing advice helpline**					
	Receive advice on safety, amount, technique, how to overcome barriers and make it fun		Knowledge, physical skills, cognitive skills, beliefs about capabilities, and beliefs about consequences	Education, incentivization, and persuasion	Instruction on how to perform the behavior, information about health consequences, information about emotional consequences, goal setting, problem solving, action planning, restructuring the physical environment, and restructuring the social environment
**Health promotion messages via mail and telephone**					
	**Postcard #0 (cling sheet)**				
		Brush 2 times every day, a tiny smear for baby, a pea size for ages 2 years to adult, use fluoride toothpaste to prevent decay, and you don’t need a lot of toothpaste to make it work	Physical skills, beliefs about consequences	Training, education	Goal setting, instruction on how to perform the behavior
	**Postcard #10 (thank you)**				
		The best way to promote oral health and prevent tooth decay is by brushing teeth with fluoride toothpaste every day two times a day. This simple step has been proven to be effective in promoting oral health and reducing tooth decay and dental care costs.	Knowledge, beliefs about consequences	Education, incentivization, coercion	Goal setting, information about health consequences, credible source, behavior cost
	**Message #1 (brush front and back)**				
		Brush the front and the back of all the teeth. Roar like a lion to reach the back of all the teeth. Say “Chee-tah!” to reach the front and sides.	Physical skills	Training	Instruction on how to perform the behavior
	**Message #2 (take turns)**				
		Take turns brushing... your child practices brushing first and then you do it to make sure all the teeth are brushed.	Cognitive skills	Training	Problem solving
	**Message #3 (sleepy)**				
		Brush in the evening after snacks before your child gets too sleepy.	Cognitive skills	Environmental restructuring	Action planning, restructuring the physical environment
	**Message #4 (bathtub)**				
		You can brush your child's teeth in the tub! It's fun!	Cognitive skills, emotion	Environmental restructuring	Action planning, information about emotional consequences, restructuring the physical environment
	**Message #5 (silly song)**				
		Sing a favorite song while brushing!	Cognitive skills, emotion	Environmental restructuring	Distraction
	**Message #6 (role model)**				
		Brush your teeth with your child. You are the best role model.	Identity	Modeling	Identification as role model
	**Message #7 (party, party)**				
		Have a family toothbrushing party!	Emotion	Persuasion	Restructuring the social environment
	**Message #8 (try, try again)**				
		Everyday is a new day to brush... twice a day!	Beliefs about capabilities, optimism	Persuasion	Verbal persuasion about capability
	**Message #9 (consequences)**				
		Brushing makes your mouth smell fresh.	Emotion, beliefs about consequences	Persuasion	Information about emotional consequences

### Test Condition

#### Components of the Intervention

Participants will receive all five components of the intervention: (1) a toothbrushing kit containing supplies and a single-page instruction sheet sent by mail to families’ homes; (2) a toll-free telephone helpline to request more toothbrushing supplies; (3) postcards with brief messages addressing common barriers and support for toothbrushing; (4) automated calls to parents’ telephones repeating these same health promotion messages; and (5) a toll-free telephone helpline to provide toothbrushing advice. Each of these components was designed in English and Spanish.

#### The Toothbrushing Kit

The kit contains supplies for adults and for children, specifically 7x .85 oz. tubes of toothpaste (1500 parts per million sodium fluoride), 3 adult-size toothbrushes, 1 toothbrush each for a child ages 4-24 months, 2-4 years, and 5-7 years. This quantity was chosen because the average family served by Advantage Dental Services has 3 or 4 children. In addition to the supplies, the kit includes a single-page removable “cling sheet” with instructions to brush twice a day with an age-appropriate amount of fluoride toothpaste depicted by illustration, and information about how to request additional supplies if needed. Each family receives three kits over the 9-month intervention period.

#### Toothbrushing Supplies Helpline

A toll-free number for requesting more toothbrushing supplies is included on all toothbrushing kits mailed to families. Bilingual, culturally competent Advantage Dental Services staff members manage the supplies helpline.

#### Toothbrushing Promotion Message Postcards

We created 9 health messages. The messages reflect three sets of factors known to influence health behavior: strong intention, necessary skills, and lack of insurmountable environmental constraints [21]. The messages are written at a sixth-grade (about 11 years old) reading level and do not contain medical or dental jargon. Each message, and the theoretical domains that inspired it, are in Table 1. As postcards, the messages are accompanied by simple line drawings or pictorial aids to increase visual appeal and parents’ comprehension of the written words [8,26]. An example message, designed to help in restructuring the physical environment, action planning, and to provide information about natural emotional consequences is, “You can brush your child’s teeth in the tub! It’s fun!” The accompanying drawing is of a child in a bubble bath having his teeth brushed by an adult. The postcard messages are mailed semimonthly during the first three months, and then approximately monthly.

#### Toothbrushing Promotion Phone Calls

A local radio celebrity, who identifies himself by his name on the prerecorded telephone message, delivered the health promotion messages described above (Table 1). We chose this strategy to increase perceived social support from a credible source for the intervention goal. The messages were modified for telephone delivery to make them more personable, personal, and to keep them brief. For example, the recommendation, “You can brush your child’s teeth in the tub! It’s fun!” was revised as, “You know, you don’t have to brush your child’s teeth at the sink all the time. Try brushing in the bathtub for something new and fun.” There are eleven telephone message calls (two repeated) that are made, semimonthly during the first three months, and then monthly.

#### Toothbrushing Advice Helpline

A toll-free number for toothbrushing advice is included on all printed materials mailed to families and in the prerecorded telephone messages. Bilingual, culturally competent Advantage Dental Services staff members manage the helpline. The staff have been trained by the University of Washington investigators to be familiar with frequently asked questions about brushing children’s teeth and using fluoridated toothpaste, and how to offer appropriate suggestions to overcome barriers to twice daily brushing.

### Active Control Condition

Participants will receive the toothbrushing kits and access to the telephone helpline for requesting additional supplies, but no additional health messages by postcard or telephone, and no access to the toothbrushing advice helpline.

### Passive Control Condition

Participants will receive the usual Advantage Dental Services practices, which may include receiving information about dental benefits via telephone and mail. This group will be on a waiting list for the trial intervention for 9 months and will then receive one toothbrushing kit. Only children less than 36 months old and their families will be included in this control condition.

By the conclusion of the study, all families will have received toothbrushing supplies. This principle, that all eligible Advantage Dental Services members will have the opportunity to benefit, is part of the organization’s mission.

### Intervention Fidelity

We plan to evaluate the fidelity of the intervention by assessing the extent to which the intervention is delivered as planned. To do so, we will confirm delivery of the toothbrushing supplies, postcards, and prerecorded telephone messages. Participants’ use of the telephone helpline or supply line will be documented, and the nature of these contacts will be analyzed by type of request.

### Study Measures and Data Collection

#### Outcomes

The primary outcome for all children less than 21 years old will be restorative dental care received as a proxy for the presence of dental caries. Additionally, for children less than 36 months old at baseline, the other primary outcome will be parent/caregiver reported frequency of twice daily toothbrushing the child’s teeth. Secondary and tertiary outcomes will be cost of dental care for all participants; and, only for children less than 36 months old at baseline, parent/caregiver-reported oral-health related quality of life of the child, satisfaction with the program, and dental caries (tooth decay).

#### Mediators and Confounders

Mediators of the effect of the intervention on the primary outcomes will be the number of toothbrushing kits and instructions (mail and telephone) delivered. Parent’s age, family size, and race/ethnicity will be considered confounders and explored for effect modification. Among children less than 36 months old, potential mediators to be examined are: parent/caregiver’s self-efficacy, attitudes, intention, skills, and norms in relation to brushing their child’s teeth. Additionally, for this group, parental educational level and child’s juice consumption will be considered confounders.

#### Data Collection

Data on type, amount, and cost of dental care will be collected through health information systems of the dental care organization (Enrollment and Claims Database) for all participants. For children less than 36 months old, information on the children’s toothbrushing behaviors, parent-rated oral health and oral health-related quality of life of the child, child’s juice consumption and frequency, parental self-efficacy, intention and attitudes regarding brushing the child’s teeth, parent educational level, and their opinions about each component of the intervention will be collected through telephone interviews with parents/caregivers at baseline and at the end of the intervention. For children less than 36 months old at baseline, information on the presence of untreated dental caries (cavitated caries in permanent or primary teeth) will be collected through a clinical examination 24 months after the study start date. Fidelity information will be obtained through examination of internal records of mailings, returned mail receipts, and telephone calls.

### Statistical Analysis

#### Sample Size

Sample size for dental care outcomes was not calculated, as the sample size of 20,000 participants was deemed sufficient to observe an effect of the intervention on the primary outcome of restorative care utilization.

Prevalence and effect size estimates for frequency of twice daily toothbrushing among children less than 36 months old at baseline was based on that reported in a study in a similar population [25]. Assuming a proportion in the passive control group of .6, alpha = .025, beta = .20, the required sample sizes for effect sizes of 50% and 40% are 39 and 66 participants in each group. We decided on a sample size of 150 participants in each group.

Untreated dental caries estimate was based on that reported in a study in a similar population [1]. Assuming a proportion of children with dental caries experience in the passive control group of .5, alpha = .025, beta = .20, the required sample sizes for effect sizes of 30% and 40% are 206 and 113. We decided on a sample size of 210 participants in each group.

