#### Statistical Analysis Plan

Descriptive statistics (means, SD, counts, and percentages) will be calculated for all variables of interest overall and stratified by age group. Difference in difference models will be used to evaluate changes in frequencies and rates for pre versus post intervention effects within the intervention groups and for passive control versus active control versus test effects. Linear regression will be used to evaluate continuous outcomes and logistic regression will be used to evaluate binary outcomes. The primary hypothesis for all participants is that the test intervention group will have a lower number of restorative dental care procedures received than the active control group during the 18 months post intervention start date. For children less than 36 months old, the primary hypothesis is that the test intervention will increase toothbrushing frequency more than the active control intervention and no change in passive control group will be observed 10 months post intervention start date. Secondary hypotheses are that member satisfaction and oral health-related quality of life of the participants will be greater and that dental care costs and dental caries will be lower in the test intervention and active control than in the passive control.

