### Trial Status

Participants were selected (N=21,743 families, 2857 with children less than 36 months old at baseline) and randomly assigned to the test (n=10,797), active control (n=10,796), and passive control (n=150 families with children less than 36 months old) conditions. A random sample of parents/caregivers of children less than 36 months old was interviewed (n=450, 150 for each test, active, and passive control conditions). The program has been deployed.

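### The toothbrushing sample size is calculated against passive control, but the primary hypothesis is test versus active control, so the stated 80% power does not belong to the primary contrast

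*Protocol article*

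**What the plan says.** **Sizing.** The Sample Size section of the protocol article begins the toothbrushing calculation with "Assuming a proportion in the passive control group of .6, alpha = .025, beta = .20" and concludes that "the required sample sizes for effect sizes of 50% and 40% are 39 and 66 participants in each group". It then states: "We decided on a sample size of 150 participants in each group". It gives no reason for 150 and no proportion for the active control. Trial Status confirms the interviewed subsample: "n=450, 150 for each test, active, and passive control conditions".

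**Hypothesis.** The Statistical Analysis Plan section says that, for children under 36 months, "the primary hypothesis is that the test intervention will increase toothbrushing frequency more than the active control intervention". Passive control enters that sentence only through the expectation that "no change in passive control group will be observed 10 months post intervention start date". The secondary hypotheses do compare both active arms with passive control, but on satisfaction, quality of life, costs and caries rather than on brushing.

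**What the arms share.** Under Active Control Condition, families get the kits and the supplies helpline. Under The Toothbrushing Kit, each kit includes a sheet that tells families to brush twice a day. Under Components of the Intervention, the test arm adds postcards, automated calls and the advice helpline.

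**The concern.** The calculation asks whether brushing differs from a passive-control rate of .6 by 24 or 30 points. The primary hypothesis asks whether messages and advice add anything to kits that both arms receive. The sized effect carries over to that question only if the kits alone do nothing. The article does not expect that: its Introduction reports that programs giving advice with free supplies, including by mail, had positive effects on parents' behaviour, twice-daily brushing included.

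At stake is how a null result is read. The Discussion says the evaluation will help decide whether the instruction and support component is needed or can be dropped, which is the test-versus-active question. A reader who takes the printed 80% power to apply to that contrast would give a null interview result more weight than it may deserve.

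**Working it through.** **Inputs from the article.** Passive-control proportion .60; alpha .025 (sidedness not stated); power .80; effect sizes 50% and 40%; 150 per arm.

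**1. Reproducing the plan's figures.** Read the effect sizes as relative increases: .60 × 1.5 = .90 and .60 × 1.4 = .84. With the pooled-variance normal formula, no continuity correction and 1:1 allocation,

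n = [z₁₋α/₂ √(2p̄(1−p̄)) + z₁₋β √(p₁(1−p₁) + p₂(1−p₂))]² / (p₂−p₁)²,

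with two-sided α = .025 (z = 2.241) and z₁₋β = 0.842:

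- .60 vs .90: (1.373 + 0.483)² / .09 = 38.3, so 39.
- .60 vs .84: (1.423 + 0.515)² / .0576 = 65.2, so 66.

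Both match. One-sided .025 would give 32 and 54. The same two-sided convention also returns the article's caries figures of 206 and 113, so the reading is secure. At 150 per arm, power for these passive-control contrasts exceeds 99%.

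**2. Power for the primary contrast.** The active-control rate is not in the article, so it is an assumption here. It is expressed as the share of the gain over .60 that the kits alone deliver: share = (active − .60) / (test − .60). Power is

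Φ{ [(p₂−p₁)√150 − 2.241 √(2p̄(1−p̄))] / √(p₁(1−p₁) + p₂(1−p₂)) }.

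Worked case, active .72 and test .84: (0.12 × 12.247 − 1.313) / 0.580 = 0.270, and Φ(0.270) = 61%.

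| Test | Active (assumed) | Share from kits | Power at 150 per arm | n per arm for 80% |
|---|---|---|---|---|
| .84 | .66 | 25% | 92% | 109 |
| .84 | .72 | 50% | 61% | 226 |
| .84 | .75 | 63% | 38% | 382 |
| .90 | .75 | 50% | 89% | 121 |
| .90 | .80 | 67% | 57% | 242 |

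**3. Break-even.** Power reaches 80% at 150 per arm only if the active rate is no higher than about .69 when test is .84, or about .77 (.7685) when test is .90. As shares these are .09/.24 = 38% and .1685/.30 = 56%.

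**4. Detectable difference.** With 150 per arm, 80% power and two-sided .025, the smallest detectable increase is about 16.5 points from an active rate of .60, 15 points from .70 and 12 points from .80.

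**5. Sensitivity to the planned analysis.** The figures above use follow-up proportions only, whereas the article plans difference-in-difference models. Take a baseline of .60 in both arms and within-child correlation ρ (both assumptions), with variance per arm [p(1−p) + .24 − 2ρ√(p(1−p) × .24)] / 150. Power at ρ = 0, .5 and .7 is then about 27%, 51% and 75% for .84 vs .72, and about 45%, 75% and 92% for .90 vs .75. Losing 20% of interviews (120 per arm; also an assumption) lowers the follow-up-only 61% to 50% and the 89% to 80%.

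**The case against.** The strongest reply is that 150 is 2.3 to 3.8 times the calculated 66 and 39, so a margin exists. That stands: if the kits deliver only a small part of the gain, or if test reaches .90 and the kits deliver half of it, power is adequate. But the article neither ties the choice of 150 to test versus active nor says what active rate it expects.

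Passive control also belongs to the research question. Aims and Objectives compares the full program with supplies alone or no intervention, and the primary hypothesis mentions the passive arm. Sizing against it is therefore incomplete rather than irrelevant.

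The decision about the messages does not rest on 450 interviews alone. The primary hypothesis for all participants, on restorative care, is also test versus active, with 10,797 and 10,796 families. This limits the consequence to how the interview result is read on its own.

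Nor can this be excused as condensation in a journal article. The article prints a calculation for one contrast and a primary hypothesis for another.

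A reader might also infer that the trial must demonstrate no change in passive control by a non-significant test, or that ordinary ageing would defeat the hypothesis. The article does not support this. It sets no such rule, and it plans difference-in-difference comparisons across all three arms.

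**Conclusion.** The mismatch is established from the article alone: the stated 80% power belongs to contrasts with a passive-control rate of .6, not to the primary test-versus-active contrast. The arithmetic behind 39 and 66 is correct.

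The size of any shortfall is conditional. Across the active rates tabulated, power at 150 per arm runs from 38% to 92%, on assumed rates, two-sided .025 and follow-up proportions. It would be tempting to conclude that the trial is underpowered. The article does not support that, because it never gives the active-control rate on which the answer turns.

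This should be fixed, but it is not a fatal defect. Enrolment and baseline interviews are complete, and what remains open is the power statement and the interpretation.

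**What to change.** 1. In Sample Size, label the 39 and 66 as applying to contrasts with passive control.
2. For test versus active, add one of three statements: the difference detectable with 150 per arm (about 12 to 16.5 points for active rates from .80 down to .60, on follow-up proportions); the sponsor's own expected active-control rate, with its power under the planned difference-in-difference analysis; or a plain statement that toothbrushing is powered only against passive control. The active rates used in this check are illustrations and should not be written in as planning values.
3. Report test minus active with its confidence interval, and say that a null interview result will not by itself be taken as showing that the messages can be dropped.

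The cost is a change of wording and a less favourable stated power. No participants are added. It should be done before the follow-up interview results are read.

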## Introduction

### The Importance of Brushing Teeth Twice a Day

Dental caries is a disease with marked socioeconomic and regional disparities. In Oregon, untreated tooth decay is twice as common in low-income children than in children from higher income families (25% vs 13%) [1]. Similarly, almost three-quarters (73%) of 6 to 9 year old children in rural Central Oregon experience tooth decay, while the statewide average is 52% [1]. Dental caries can be prevented through regular toothbrushing with fluoridated toothpaste [2-5]. The American Academy of Pediatric Dentistry and the American Dental Association recommend that toothbrushing should be performed twice daily with a fluoride toothpaste and a soft toothbrush initially by the parent, and eventually by the child [6,7]. Relatively few parents and children fully follow this recommendation [8].

Successful behavioral interventions focus on helping people acquire skills and motivation to change behavior; they are sustained and comprehensive; and, they engage peers and family members to help maintain motivation [9]. Toothbrushing beginning in infancy is a good candidate behavior. It is similar to other mildly intrusive caregiving behaviors that parents accept learning, and infants grow to tolerate. Parents’ confidence to carry out this behavior is the best predictor of being caries free at age 4 [10,11]. Once established, childhood toothbrushing habits persist [12,13], but need to be reinforced.

Toothbrushing promotion programs that provide advice, free toothpaste, and toothbrushes at a child health visit and/or by mail have shown positive effects on parents’ behaviors, including the frequency of twice daily toothbrushing of their children [14]. When accompanied by social support and in-person instruction, toothbrushing promotion programs show decreases in childhood caries and improved oral hygiene [15-17]. A program similar to that designed for the intervention study described here led to increased frequency of toothbrushing at home [17], and a 30% reduction in tooth decay [16].

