#### Recruitment

Participants will be identified through an electronic search of the enrollment database of Advantage Dental Services. All Advantage Dental Services members meeting the eligibility criteria will be included. The intervention will be delivered to all children less than 21 years old, but the evaluation of parent-reported twice daily toothbrushing and dental caries outcomes will focus on children less than 36 months old. Advantage Dental Services decided to focus on these children because of the Healthy People 2020 objective OH-1.1 to, "Reduce the proportion of children age 3 to 5 years with dental caries experience", the belief in the lifelong benefit of establishing toothbrushing habits in early childhood, and the cost implications of providing care for children this age who experience tooth decay. Because of all this, a random subsample of parents/caregivers of children less than 36 months old and a random subsample of children less than 36 months old will be recruited. Parents/caregivers of children less than 36 months old to be interviewed will be recruited through telephone calls. Children less than 36 months old to be clinically examined will be recruited at community settings such as Head Start and the Special Supplemental Nutrition Program for Women, Infants, and Children. The parents/caregivers will have the quality improvement project explained to them and have the opportunity to opt out of the evaluation.

The University of Washington Institutional Review Board reviewed this study. Consistent with US Federal regulations, participants of this quality improvement project do not meet the criteria to be considered research subjects. University of Washington personnel will have access only to deidentified data.

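### The caries sample size assumes a 50% rate of caries experience, but the planned examination records untreated cavitated decay, so the stated 80% power does not apply to that secondary outcome

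*Protocol article*

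**What the plan says.** All places are in the protocol article.

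- **Sample Size** introduces the input as a rate of untreated decay: "Untreated dental caries estimate was based on that reported in a study in a similar population [1"]. The next sentence sets a different quantity: "Assuming a proportion of children with dental caries experience in the passive control group of .5". It continues "alpha = .025, beta = .20, the required sample sizes for effect sizes of 30% and 40% are 206 and 113" and settles on 210 children per group.
- **Data Collection** describes the measurement, made 24 months after study start: "information on the presence of untreated dental caries (cavitated caries in permanent or primary teeth) will be collected through a clinical examination".
- **Outcomes** places caries among the secondary and tertiary outcomes, without saying whether treated disease counts: "satisfaction with the program, and dental caries (tooth decay").
- **The Importance of Brushing Teeth Twice a Day** cites the same reference for two kinds of rate. For untreated disease: "untreated tooth decay is twice as common in low-income children than in children from higher income families (25% vs 13"%). For disease experienced: "almost three-quarters (73%) of 6 to 9 year old children in rural Central Oregon experience tooth decay, while the statewide average is 52"%.
- **Statistical Analysis Plan** gives the secondary hypothesis that caries will be lower in the test and active control groups than in the passive control.
- **Trial Status** reports 150 families randomized to the passive control.

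**The concern.** Caries experience counts any child who has had decay, treated or not. Untreated decay counts only children with a cavity still open on the examination day. The second group is part of the first, so its rate can only be equal or lower. A lower base rate with the same relative reduction gives a smaller absolute difference and less power.

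The sample size is therefore worked out for one outcome while the examination is described for another. A null caries result could be read as evidence of no effect when the study had little chance of detecting the reduction it was sized for.

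There is also a question of meaning, separate from power. A child whose cavity has been filled has no untreated decay. Restorative care received is a primary outcome that the intervention is meant to change. A group difference in untreated decay alone could reflect differences in treatment as well as in disease.

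**Working it through.** **Inputs.** From Sample Size: control rate .5, relative reductions 30% and 40%, alpha .025, power .80, 210 per group. From the Introduction: untreated decay .25 in low-income children. Base rates .30, .35 and .40 are assumptions used to show the range. Sidedness is not stated; the two-sided reading is used because it reproduces the stated sizes.

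**Step 1: reproduce the stated sizes.** Pooled two-proportion formula, no continuity correction, p̄ = (p1 + p2)/2:

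n = [2.2414·√(2p̄(1−p̄)) + 0.8416·√(p1(1−p1) + p2(1−p2))]² / (p1−p2)²

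- .50 vs .35: (1.5670 + 0.5816)² / 0.0225 = 205.2, so 206.
- .50 vs .30: (1.5529 + 0.5708)² / 0.04 = 112.8, so 113.

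Both match. One-sided alpha gives 170 and 93, and a continuity correction gives 219 and 123, so neither was used.

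**Step 2: same formula, untreated rate .25.**

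- .25 vs .175: (1.2967 + 0.4848)² / 0.005625 = 564.3, so 565 per group.
- .25 vs .15: (1.2679 + 0.4724)² / 0.01 = 302.9, so 303 per group.

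**Step 3: power at 210 per group.** Power = Φ[(d − 2.2414·SE0)/SE1], where d = p1 − p2, SE0 is the pooled and SE1 the unpooled standard error.

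- Stated design, .50 vs .35: (0.15 − 2.2414×0.04824)/0.04768 = 0.878, power 81.0%.
- .25 vs .175: (0.075 − 2.2414×0.03992)/0.03975 = −0.364, power 35.8%.
- .25 vs .15: (0.10 − 2.2414×0.03904)/0.03873 = 0.323, power 62.7%.

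| Base rate | Power, 30% reduction | Power, 40% reduction |
|---|---|---|
| .25 | 36% | 63% |
| .30 | 45% | 74% |
| .35 | 54% | 83% |
| .40 | 64% | 90% |
| .50 (as stated) | 81% | 98% |

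At base .25, the smallest relative reduction detectable with 80% power is about 47%.

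**Step 4: passive-control number.** Reaching 210 children from 150 families needs 210/150 = 1.4 eligible examined children per family. With one child per family (150 vs 210), the same power formula, with p̄ weighted by group size, gives 31% and 55% at base .25 for the two reductions. At base .5 it gives 73% for a 30% reduction.

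**Step 5: age.** Children under 36 months at baseline, examined 24 months after study start, will be about 2 to under 5. The experience rates in the Introduction are for ages 6 to 9, and the 25% has no stated age. The article gives no caries rate of either kind for ages 2 to under 5.

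**The case against.** The strongest reply is that 36% is not a known property of this trial. The 25% is an Oregon figure for low-income children, with no age given and not specific to the three counties. The article itself reports more decay experience in rural Central Oregon than statewide. As an illustration only, scaling .25 by 73/52 gives about .35, where power is 54% and 83%. This stands, and it is why power has to be shown as a range. It does not rescue the stated figure: for the 30% reduction that led to 210, power is still only 64% at a base rate of .40. For a 40% reduction, power is adequate from about .35 upward.

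Other replies also stand in part:

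- Caries is a secondary or tertiary outcome, so no primary conclusion rests on this calculation.
- The article does not say the examination records nothing besides untreated decay, and a condensed article may omit codes. Claims data will also capture treated disease. The sections still need to agree.
- The national objective in the Recruitment section, "Reduce the proportion of children age 3 to 5 years with dental caries experience", explains the choice of age group. It does not define the trial's outcome.

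A reader might infer that the .5 was taken from the 52% statewide figure. The two are close, but the article does not say so and the source is not at hand.

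**Conclusion.** The concern holds as a mismatch between the sample-size input and the outcome described, of moderate weight. The stated 80% power applies to an outcome with a 50% base rate. For untreated cavitated decay at 210 per group, power for a 30% reduction runs from about 36% to 64% over base rates .25 to .40, and for a 40% reduction from about 63% to 90%. It is lower if the passive control yields only 150 children.

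These figures assume two-sided alpha .025, comparison of each active group with the passive control, independent children and no losses. Examining siblings to reach 210 would strain the independence assumption.

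Three stronger readings are tempting and not supported. The sample-size arithmetic is not wrong: it reproduces exactly. The trial's primary hypotheses are not underpowered on this account, since they concern restorative care and toothbrushing frequency. And a single power of 36% cannot be asserted, because the untreated rate in these children is not in the document.

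**What to change.** 1. Reconcile the Outcomes, Data Collection and Sample Size sections on one definition of the caries outcome.
2. Restate power over a range of base rates plausible for children aged 2 to under 5, for both reductions, and give the source and age of each rate. State the sidedness of alpha.
3. Use the passive-control number actually available. If more than one child per family is needed to reach 210, say so and allow for correlation within families.
4. Preferably, also score filled teeth and teeth missing because of caries at the examination planned for July 2016, so that caries experience can be analysed alongside untreated decay. This separates disease from treatment received. It does not by itself justify .5 at these ages or restore 80% power: with 150 passive-control children, power for a 30% reduction is 73% even at .5.

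The cost is a few extra examination codes, a short rewrite and a less favourable power statement. No extra children are needed for these changes.
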